### 13.1.2 Phase II Trial

The primary endpoint of the phase II trial will be the rate of complete/near-complete pathologic response ( $\geq 95\%$  tumor necrosis) following treatment with this multimodality therapy. Anticipating an improvement in the pathological complete/near-complete response rate from 10% with RT alone to 33% with combined sorafenib and RT, we will have an 80% power to detect this difference if we accrue 25 patients, assuming a type I error rate of 5%.

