### 1.5 Treatment-Induced Pathologic Necrosis

When used as monotherapy, preoperative RT has rarely been observed to lead to significant rates of complete or near-complete pathological response. Two single institution series have reported rates of 80% tumor necrosis in approximately 30% of patients. However, few complete (100% tumor necrosis) or near-complete ( $\geq 95\%$  tumor necrosis) pathologic responses were observed, and, although limited and retrospective, the data suggest that  $< 95\%$  tumor necrosis is not associated with significant improvements in clinical endpoints, such as local-disease control, distant-disease control, or overall survival.

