## 2.0 STUDY DESIGN

This is a phase I/II, open label, non-randomized study of neoadjuvant conformal radiotherapy plus sorafenib for patients with extremity STS high grade greater than 5 cm in

maximal dimension or low grade greater than 8 cm in maximal dimension.

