#### 4.0 ACCRUAL GOAL

- Phase I— Dose-escalation schedule comprising 6 to 12 patients (see schema). This sample size is based on a traditional 3+3 cohort design with escalating doses of sorafenib in combination with 50 Gy of conformal radiotherapy delivered in 25 fractions (200 cGy per fraction). Based on preclinical data regarding the radiobiology of sorafenib, sorafenib will be initiated at a dose of 200 mg twice daily, followed by 200 mg Q AM/400 mg Q PM for the 2nd cohort, followed by 400 mg bid for the 3rd cohort. Since 400 mg bid is the well established MTD for sorafenib monotherapy in patients with renal cell carcinoma and hepatocellular carcinoma, the dose will not be escalated above this level even if DLT is not observed. Dose level escalation will be determined based on DLTs observed from initiation of sorafenib/RT until time of surgery.
- Phase II— anticipated number of 25 patients will be enrolled depending on phase I result. Anticipating an improvement in near-complete pathological response ( $\geq 95\%$  tumor necrosis) from 0% with RT alone to 33% with combined sorafenib and RT, we will have an 80% power to detect this difference if we accrue 25 patients, assuming a type I error rate of 5%.

Total target accrual is 30-35 patients depending on results of dose-escalation schedule from Phase I of trial.

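### The Phase II null response rate is 0% in Section 4.0 and 10% in Section 13.1.2 for the same 25 patients and 80% power; the two imply different bars, and 80% is wrong for the 0% null

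*Protocol*

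**What the plan says.** Two current sections of the Protocol state the Phase II design assumption for the same primary endpoint, tumor necrosis of at least 95%.

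- Section 4.0 (Accrual Goal) anticipates an improvement "from 0% with RT alone to 33% with combined sorafenib and RT, we will have an 80% power to detect this difference" with 25 patients and a 5% type I error rate.
- Section 13.1.2 (Phase II Trial) starts its sizing statement with "Anticipating an improvement in the pathological complete/near-complete response rate from 10% with RT alone to 33% with combined sorafenib and RT", and gives the same power, number of patients and type I error rate.

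Section 2.0 describes an "open label, non-randomized study of neoadjuvant conformal radiotherapy plus sorafenib", so there is no concurrent radiotherapy-alone group. Section 1.5 gives the background for that rate. It says that with preoperative radiotherapy alone "few complete (100% tumor necrosis) or near-complete" responses were observed, and it gives no percentage at the 95% cut-off. Neither sizing statement gives the test, its sidedness or a number of responders. The pause after 10 Phase II patients is a safety assessment and adds no efficacy look.

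**The concern.** In a single-arm trial with a binary endpoint, the null rate determines how many responders are needed to conclude that the treatment does better than the comparator. Here it has two values. A result of 1 to 5 responders in 25 would reject a null of 0% but would not reject a null of 10% at one-sided 5%. A reader of the protocol cannot tell which applies to the primary endpoint. A statistical analysis plan can add the test and the cut-off, but it cannot make two rates in the protocol agree.

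The same power and sample size attached to two such different nulls also suggests that at least one of the statements was not calculated from the rate beside it.

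**Working it through.** **Inputs.** n = 25, target p1 = 0.33, power 80% and type I error 5% (Sections 4.0 and 13.1.2); p0 = 0 (Section 4.0) or p0 = 0.10 (Section 13.1.2). Assumption: a one-sample test of the response rate against a fixed p0. Sidedness is not stated, so both are tried. X is the number of responders.

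**Step 1. Reproduce the stated 80% for 10% versus 33%.** One-sided 5% normal approximation with the variance taken at 33%:

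- Standard error = √(0.33 × 0.67 / 25) = 0.0940
- 0.23 / 0.0940 = 2.45; 2.45 − 1.645 = 0.80; power = Φ(0.80) = 78.8%
- n for 80% power = (1.645 + 0.842)² × 0.2211 / 0.23² = 25.8, so 26

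This is close to the stated 80% with 25 patients.

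**Step 2. Exact binomial, p0 = 10%, n = 25.**

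| Rule | P(reject) at 10% | Power at 33% |
|---|---|---|
| X ≥ 5 | 9.8% | 95.0% |
| X ≥ 6 | 3.3% | 88.1% |
| X ≥ 7 | 0.9% | 76.8% |

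The smallest cut-off with one-sided alpha of at most 5% is 6 of 25, with power 88.1%. If the upper tail is held to 2.5% (an equal-tail two-sided 5% test), the cut-off is 7 of 25 and power is 76.8%. A two-sided exact test that orders outcomes by their probability behaves differently: P(X = 0 | 0.10) = 0.9^25 = 0.072 exceeds P(X = 6 | 0.10) = 0.024, so no lower-tail outcome is added, the p-value at 6 of 25 stays at 0.033, and the cut-off stays at 6.

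Other approximations at n = 25 (one-sided / two-sided):

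- Normal with null variance: 91.9% / 88.4%
- The same with continuity correction: 88.2% / 83.7%
- Arcsine: 89.6% / 82.7%
- Normal with the variance at 33%: 78.8% / 68.6%

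**Step 3. Exact binomial, p0 = 0%, n = 25.** Any response is impossible under this null, so X ≥ 1 rejects with alpha 0.

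- Power at 33% = 1 − 0.67^25 = 99.996%
- Four patients: 1 − 0.67^4 = 79.8%; five patients: 1 − 0.67^5 = 86.5%
- Normal approximation with the variance at 33%, n = 25: 96.9% one-sided, 93.9% two-sided; with continuity correction, 95.1% and 90.9%

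No single-arm calculation comes near 80%. A two-arm, two-sided, continuity-corrected formula does give 25 for 0% versus 33%, but that is 25 per arm and this trial has one arm. The protocol does not say that this formula was used.

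**Step 4. Consequence.** If the true rate were 10%, which is Section 13.1.2's own figure for radiotherapy alone, the chance of at least one response in 25 would be 1 − 0.9^25 = 92.8%. The chance of at least six would be 3.3%.

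**The case against.** The strongest reply is that Section 13 is the formal statistical section, that its 10% versus 33% statement works with 25 patients, and that the 0% in the accrual section changes neither enrolment nor patient risk. The Phase II objective in Section 3.1 is to determine a rate, and the test and cut-off may stand in an analysis plan that is not shown. Much of this is fair: the absence of a test or cut-off from the protocol is not itself a fault, and the arithmetic error is confined to Section 4.0. It does not remove the conflict. Both sections are current, neither defers to the other, and both frame the design as a test with a type I error rate and power.

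Four stronger readings are tempting and are not supported.

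- A reader might infer that 80% fits neither null. For 10% it is approximately reproduced in step 1, and most other methods give more than 80%.
- A reader might infer that Section 4.0 declares 1 of 25 a success. It states no threshold. That bar, and the 92.8% in step 4, follow from testing against 0%, not from a written rule.
- A reader might infer that a two-sided 5% level forces 7 of 25 and 76.8% power. Among exact tests this holds for an equal-tail rule only.
- A reader might infer that Section 1.5 establishes 10%. Its wording fits poorly with exactly 0%, but it gives no figure for 10% either.

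**Conclusion.** The point holds. The protocol gives two incompatible null rates for the Phase II primary endpoint, and they imply bars of 1 of 25 and 6 of 25 (exact, one-sided 5%). The 80% power statement is wrong for the 0% null, where exact power exceeds 99.9%. For the 10% null it is approximately right under one normal approximation (78.8%) and conservative under the exact one-sided test (88.1%). Exact power drops to 76.8% only if 2.5% is required in the upper tail.

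These figures assume a one-sample test with all 25 patients evaluable and no interim efficacy look. Which null rate is correct cannot be settled from the protocol. The finding does not show that 25 patients are too few. Because this is the primary endpoint, the rate and the threshold should be fixed before results are known.

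**What to change.** 1. Use one radiotherapy-alone rate in Sections 4.0 and 13.1.2, and cite its source. The 10% in Section 13.1.2 is the workable candidate because 25 patients suit it, but the sponsor must confirm it.
2. Delete the statement in Section 4.0 that pairs 0% with 80% power.
3. Restate the power with its test, sidedness and responder threshold. If 10% is confirmed, this could read: exact one-sided binomial test at 5% of a response rate of at most 10%; treatment considered promising if at least 6 of 25 patients have at least 95% necrosis; actual alpha 3.3%, power 88% at 33%.
4. If a two-sided test is intended instead, name the exact method, because the cut-off (6 or 7 of 25) and the power (88.1% or 76.8%) depend on it.

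The cost is two sentences in an amendment and the citation of a source. No extra patients are needed.

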#### Treatment Stop Rule

A pause in study accrual will be implemented in the phase II portion of the trial after 10 patients have completed concurrent sorafenib plus conformal radiotherapy followed by surgical resection. Safety assessment will be made 6 weeks following resection of the 10th patient (9 – 13 weeks following completion of concurrent sorafenib and RT) to ensure that excess DLTs are not observed. The study will be **terminated for safety** (not lack of efficacy) if 4 of these 10 patients experience grade 3 adverse events or greater since this would represent an increase from the baseline rate of serious AEs expected from the standard combination therapy of preoperative radiation and surgical resection. This pause in accrual will allow us to review all safety data collected to date. If DLTs in excess of our stopping rule are not observed, then the phase II trial will continue to the targeted accrual of 25 patients.

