#### Treatment Stop Rule

Furthermore, a pause in study accrual will be implemented in the phase II portion of the trial after 10 patients have completed concurrent sorafenib plus conformal radiotherapy followed by surgical resection. Safety assessment will be made 6 weeks following resection of the 10th patient (9 – 13 weeks following completion of concurrent sorafenib and RT) to ensure that excess DLTs are not observed. The study will be ***terminated for safety*** (not lack of efficacy) if 4 of these 10 patients experience grade 3 adverse events or greater since this would represent an increase from the baseline rate of serious AEs expected from the standard combination therapy of preoperative radiation and surgical resection. This pause in accrual will allow us to review all safety data collected to date. If DLTs in excess of our stopping rule are not observed, then the phase II trial will continue to the targeted accrual of 25 patients.

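### Phase II accrual already pauses after 10 resected patients, and stopping there if none has responded would cost under one point of power

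*Protocol*

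**What the plan says.** Protocol 13.1.2 makes necrosis of 95% or more in the resected tumour the phase II endpoint: "The primary endpoint of the phase II trial will be the rate of complete/near-complete pathologic response". The target is an improvement "from 10% with RT alone to 33% with combined sorafenib and RT", and the section adds: "we will have an 80% power to detect this difference if we accrue 25 patients, assuming a type I error rate of 5" percent. It names no test, sidedness or number of responders that would count as success.

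The Treatment Stop Rule, worded alike in 7.1 and 13.1.2, halts accrual "after 10 patients have completed concurrent sorafenib plus conformal radiotherapy followed by surgical resection". The assessment falls 6 weeks after the tenth resection and covers safety data. The study ends for safety, "not lack of efficacy) if 4 of these 10 patients experience grade 3 adverse events or greater". If the safety limit is not exceeded, "then the phase II trial will continue to the targeted accrual of 25 patients".

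Section 7.6 has the percentage of necrosis determined on the resected specimen, from about 10 to 15 sections per tumour, with central review of the slides. No turnaround time is given. The protocol contains no futility rule.

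**The concern.** A single-stage design is usually defended on two grounds: an interim look interrupts accrual, or the endpoint matures too late to be useful. Neither applies well here. Accrual is already interrupted, and the endpoint is fixed at surgery, which all 10 patients have had by the pause. Yet the only route out of the pause other than continuing to 25 is the safety limit.

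At stake are up to 15 further patients who would receive an investigational drug on top of preoperative radiotherapy before curative surgery, when the first 10 gave no sign of the response sought. Section 1.2 cites a 35% wound complication rate for preoperative radiotherapy, and the Synopsis calls the safety and efficacy data on the combination limited.

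**Working it through.** **Inputs.** From 13.1.2: reference rate p0 = 10%, target p1 = 33%, N = 25, type I error 5%, power 80%. From the Treatment Stop Rule: pause at n1 = 10. The number of responders r needed for success is not stated, so r = 6 and r = 7 are both assumptions. The calculations are exact binomial and leave the safety stop out of both columns.

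**1. The plan's own figure.** With X ~ Bin(25, p), the type I error is P(X ≥ r | 0.10) and the power is P(X ≥ r | 0.33).

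| r | Type I error | Power |
|---|---|---|
| 5 | 9.80% | 95.0% |
| 6 | 3.34% | 88.1% |
| 7 | 0.95% | 76.8% |

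r = 6 is the smallest value within a one-sided 5%, and r = 7 the smallest within 2.5%. The smallest exact N for 80% power is 19 at one-sided 5% and 23 at 2.5%. An unpooled Wald calculation, one-sided, gives 78.8% at N = 25. The stated 80% with 25 patients is therefore of the right size.

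**2. Chance of no responders in 10.** P(0/10) = (1 − p)^10, and expected N = 10 + 15 × [1 − P(0/10)].

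| True rate | P(0/10) | Expected N |
|---|---|---|
| 10% | 0.90^10 = 34.9% | 10 + 15 × 0.651 = 19.8 |
| 20% | 0.80^10 = 10.7% | 10 + 15 × 0.893 = 23.4 |
| 33% | 0.67^10 = 1.8% | 10 + 15 × 0.982 = 24.7 |

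**3. Effect of stopping at 0/10.** The stop removes only those trials that start 0/10 and would still have reached r among the remaining 15:

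P(success with stop) = P(X ≥ r) − (1 − p)^10 × P(Y ≥ r), with Y ~ Bin(15, p).

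- r = 6, p = 0.10: 0.0334 − 0.3487 × 0.0022 = 0.0326
- r = 6, p = 0.33: 0.8813 − 0.0182 × 0.3709 = 0.8746
- r = 7, p = 0.10: 0.0095 − 0.3487 × 0.0003 = 0.0094
- r = 7, p = 0.33: 0.7679 − 0.0182 × 0.1951 = 0.7643

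The subtracted term is never negative, so the stop cannot raise the type I error.

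**4. What 0/10 would mean.** The one-sided 95% upper limit is 1 − 0.05^(1/10) = 25.9%, below the 33% target. The chance of still reaching 6/25 is 0.2% at a true rate of 10%, 6.1% at 20% and 37.1% at 33%.

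**5. A stricter boundary, for comparison.** Stopping at 1 or fewer of 10 gives power of 82.2% (r = 6) or 73.1% (r = 7) and stops 10.8% of trials at a true rate of 33%. That is a real cost, and this boundary is not proposed.

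**The case against.** **It is a legitimate design.** A single-stage trial of 25 with a safety-only pause is acceptable, the omission looks deliberate, and the stated power is of the right size. That stands: nothing here is an arithmetic error.

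**A reader might infer that the rule forbids using the necrosis results.** The text does not go that far. The parenthesis on lack of efficacy can be read simply as naming the ground for the safety termination, and nobody is barred from reading the slides. What the text does fix is that safety is the only stated stopping ground and that accrual otherwise continues.

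**A reader might also infer that every necrosis result is certainly in hand at the pause.** That is likely from the timing but not documented, since 7.6 requires central review and states no turnaround.

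**The power figures rest on a rule the protocol does not contain.** True, and a statistical analysis plan that is not shown may supply one. Both plausible values are therefore given. With 7/25 the power is below 80% even without the look.

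**The reference rate is unsettled.** Section 4.0 gives an improvement "from 0% with RT alone to 33% with combined sorafenib and RT", in conflict with 13.1.2. If the reference really were 0%, any responder would reject it. Power at 33% would then fall from about 100% to 1 − 0.67^10 = 98.2%, a cost of 1.8 points, and true rates of 10% or 20%, both improvements on 0%, would be stopped 35% and 11% of the time. That conflict is a separate point; the sizes here use the 10% rate.

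**The benefit is modest and has a price.** At a true rate of 10% the rule lets 65% of trials continue and saves about 5 patients on average (25 − 19.8). Stopping would also cut short the DCE-MRI comparison, which 13.2.2 sizes on 25 patients with 71% stated power, and the other secondary objectives. This stands as the main cost.

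**Conclusion.** A worthwhile, inexpensive improvement rather than a correction. At a pause the protocol already schedules, it would continue to 25 after 0/10 responders as long as the safety limit is not reached. Under the 10% reference rate, a stop at 0/10 costs 0.7 points of power with an assumed 6/25 rule and 0.4 points with 7/25. The type I error falls slightly (3.34% to 3.26% with 6/25).

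These figures assume exact binomial testing and that all 10 necrosis results are read before accrual restarts. It would be too strong to say that 0/10 proves the regimen inactive: at a true 33% it would happen 1.8% of the time, and 37% of those trials would still reach 6/25. Section 1.5 itself calls the evidence for the 95% threshold limited and retrospective.

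**What to change.** Leave the safety rule and its wording as they are, including the parenthesis. Add a separate sentence to the Treatment Stop Rule in both 7.1 and 13.1.2, for example: *Separately, and even if the safety limit is not exceeded, accrual will not resume if none of the first 10 phase II patients has at least 95% tumor necrosis.*

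In 13.1.2, state the two-stage operating characteristics for whichever final critical value the sponsor adopts, after settling which reference rate applies.

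The cost is under one point of power at the 10% reference rate, with no extra patients or visits. The restart would wait for pathology only if central review takes longer than the 6 weeks already allowed. If the stop is triggered, the DCE-MRI, biomarker and other secondary objectives end with about 10 phase II patients; the sponsor should accept this openly when adopting the rule.

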### 13.2 Secondary Objectives

13.2.1 To determine the rate of R0 (negative resection margin), R1 (microscopically positive resection margin), and R2 (macroscopically resection margin) following neoadjuvant conformal radiotherapy in combination with sorafenib.

13.2.2 To analyze changes in tumor blood flow, blood volume, capillary permeability, and cell viability pre- and post-treatment with combined sorafenib/RT using dynamic contrast-enhanced MRI. The primary endpoints of these studies will be the transfer constant (Ktrans) and the initial area under the gadolinium concentration time curve (IAUGC, mMgD°min—see **section 9.1 for DCE-MRI imaging protocol**).

To account for within-subject correlation, we will use a mixed effects model to analyze changes in DCE-MRI pharmacokinetic parameters (Ktrans and ve) at baseline and then following neoadjuvant sorafenib/RT. These

comparisons will be made within the framework of the mixed effects model. Galbraith et al. reported the mean (range) to be 0.43 ml/ml/min (0.07-1.03) for  $K^{\text{trans}}$  and 32.2 ml/ml (12.9-62.4) for  $v_e$  among human tumors. If we assume that the range represents  $\pm 2$  SD, SD is approximately 0.24 for  $K^{\text{trans}}$  and 12.38 for  $v_e$ . A sample size of 25 patients will provide 71% power to detect a 1.0 standard deviation change in  $K^{\text{trans}}$  and  $v_e$  between these two time points.

13.2.3 To initiate analyses of molecular markers of tumor response assessment comparing (1) a microarray of a panel of serum angiogenic markers pre- and post-treatment; and (2) immunohistochemistry of tumor tissue pre- and post-treatment for expression of angiogenic proteins (VEGF, VEGFR1-3), growth factors correlated with hypoxia and resistance to radiation (EGF, FGF, HIF-1 $\alpha$ ), and modulators of proliferation and signal transduction (Ki-67, pERK). These analyses will be conducted in an exploratory manner with the aim of generating clinically and biologically interesting hypotheses. We will correlate pre- and post-treatment tissue and plasma biomarker levels (as well as the pre- and post-treatment changes) with DCE-MRI parameters and clinical outcomes. A regression analysis will be used to assess a correlation with DCE-MRI parameters. Logistic regression analysis will be used for binary clinical outcomes (e.g.,  $\geq 95\%$  necrosis) and Cox regression analysis will be used for time-to-event outcomes.

13.2.4 To obtain preliminary data regarding local disease control, distant disease control, progression-free survival, and overall survival with this novel therapeutic regimen. Kaplan-Meier method will be used to estimate time-to-event measures. For definitions of time-to-event measures, see Section 11.4

13.2.5 To determine the rate of radiographic response to neoadjuvant sorafenib/RT. Cross-sectional radiographic response will be evaluated by RECIST criteria (**see section 11.3**). Categorical differences in these data (complete response, partial response, stable disease, and progressive disease) will be tested against pathologic response categories using the Chi-squared/Fisher's exact test.

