## 9.0 CORRELATIVE/SPECIAL STUDIES

### 9.1 DCE-MRI

Subjects will undergo DCE-MRI scanning at baseline and at week 7 – 9. (approximately 2 – 4 weeks post-sorafenib/RT and approximately 1 – 3 weeks pre-surgery). Baseline DCE-MRI is to be performed 1 – 3 weeks before day 1 of treatment with sorafenib/RT.

DCE-MRI will be performed at the UC Davis Advanced Imaging Research Center. Following pilot scanning, DCE T1-weighted MRI will be performed using a 3D fast spoiled-GRASS (FSPGR) pulse sequence to acquire over the time course 50 sets of images of the tumor. The other parameters are: TE = 2.3 ms, TR = 7.0 ms, 30° flip angle, 22 cm FOV, 256x64 matrix size. We expect each volumetric data set to contain about 25 image slices with 3 mm slice thickness, resulting in temporal resolution of 11.2 s for the time course data. Thus, the total scanning time for DCE MRI is expected to be less than 10 min. The Gd-based CR (0.1 mmol/kg dosage) will be delivered intravenously at 2 mL/s by a programmable power injector (Medrad, Indianola, PA) at the beginning of the third data set acquisition. The images of the first two data sets will be the baseline for the time courses. Conventional images will be taken with standard pulse sequences. We anticipate the total time in the scanner to be less than one hour.

Data will be transferred anonymously to off-line workstations and analyzed using the shutter-speed software package, which is written in the Matlab language. This program makes use of the two(or three)-water-site-exchange model and allows us to extract and pixel-by-pixel map pharmacokinetic parameters, such as  $K^{\text{trans}}$ ,  $v_e$ , and  $\tau_i$ , the mean intracellular water molecule lifetime. The computation of the average  $K^{\text{trans}}$  and  $v_e$  and  $\tau_i$  values from the lesion region-of-interest (ROI) and parametric mapping of  $K^{\text{trans}}$  and  $v_e$  and  $\tau_i$  will be performed with both the FXL and FXR models.

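### The 71% power stated for a 1.0 SD change in the DCE-MRI parameters does not reproduce for the within-patient comparison described (92% or more under ordinary assumptions), and the modelled parameters do not match the named imaging endpoints

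*Protocol*

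**What the plan says.** Protocol section 13.2.2 covers the DCE-MRI secondary objective. On power it states: "A sample size of 25 patients will provide 71% power to detect a 1.0 standard deviation change in" each of two parameters, which are Ktrans and v_e. The change meant is the one "between these two time points". They are the two scans in section 9.1: "Subjects will undergo DCE-MRI scanning at baseline and at week" 7 to 9. The analysis is described as follows: "To account for within-subject correlation, we will use a mixed effects model to analyze changes in DCE-MRI pharmacokinetic parameters", namely Ktrans and v_e.

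The SDs come from a published range of values among human tumours, introduced by "If we assume that the range represents" plus or minus 2 SD. This gives 0.24 for Ktrans and 12.38 for v_e. No alpha, sidedness or pre/post correlation is given for this calculation. The only type I error rate in section 13 belongs to the pathologic response endpoint in 13.1.2 ("assuming a type I error rate of 5"%).

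On endpoints, the same section says "The primary endpoints of these studies will be the transfer constant", that is Ktrans, and it names a second one beside it: "the initial area under the gadolinium concentration time curve", or IAUGC. Section 3.2 names the same pair.

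**The concern.** A change of 1.0 SD measured twice in the same 25 patients is a large effect for a paired design, and 71% looks far too low for it. The effect size, the power or the unstated assumptions must differ from what the sentence says. A reader who takes it at face value will think the imaging study is only moderately able to detect a change of 0.24 in Ktrans, which is 56% of the quoted mean (0.24/0.43). A null imaging result could then be read as lack of power when it would in fact be informative.

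The section also names one pair of endpoints and gives the model, SDs and power for another. IAUGC is called primary but has no stated analysis there, while v_e is modelled and powered without being named as an endpoint. The protocol should say which pair carries the imaging objective.

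**Working it through.** **Inputs.** n = 25, an effect of 1.0 SD and a stated power of 71% (section 13.2.2). Two scans per patient (section 9.1). SDs from the published range (section 13.2.2). Assumed, because not stated for this objective: two-sided alpha of 5% and a pre/post correlation ρ between 0 and 0.5.

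**Step 1: the SDs.** Range divided by 4:
- Ktrans: (1.03 − 0.07)/4 = 0.24
- v_e: (62.4 − 12.9)/4 = 12.375, given as 12.38

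Both reproduce. They describe spread between tumours, so they are between-patient SDs and not SDs of a within-patient change.

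**Step 2: the stated 71%.** With standardised effect d on the paired differences, power is approximately Φ(√n·d − 1.96). The exact value uses the noncentral t with 24 degrees of freedom and noncentrality √n·d.

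*SD read as the SD of the change:* d = 1.0 and √25 × 1.0 = 5.
- Normal: Φ(5 − 1.96) = 99.9%
- Exact t: 99.8%

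*SD read as the between-patient SD:* the SD of a difference is SD·√(2(1 − ρ)), so d = 1/√(2(1 − ρ)).

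| ρ | d | Normal | Exact t |
|---|---|---|---|
| 0 | 0.707 | 94.2% | 92.4% |
| 0.25 | 0.816 | 98.3% | 97.5% |
| 0.5 | 1.000 | 99.9% | 99.8% |

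Neither reading gives 71%.

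**Step 3: what would give 71% at 1.0 SD?** With the between-patient SD and two-sided 5%:
- The correlation would have to be about −0.82 (exact t) or −0.98 (normal), which is implausible for repeat scans of one tumour.
- Alpha of 0.025, as in a split over two parameters, still gives 86.6% at ρ = 0 (exact t). Alpha of 0.01 gives 76%.
- Ignoring the pairing and treating the scans as two independent samples of 25 gives 94.2% (normal) or 93.4% (t).

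With the SD of change, 8 patients already give 68% and 9 give 75% (exact t).

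**Step 4: possible sources.** Two routes come close to 71%, both by normal approximation:
- A paired change of 0.5 SD of the differences: Φ(5 × 0.5 − 1.96) = 70.5%. Exact t gives 67.0%.
- A 1.0 SD difference between two independent groups of 12.5: 70.5%. Exact t with 12 against 13 gives 66.7%. This is not the comparison described.

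**Step 5: endpoints side by side.**

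| Place in the Protocol | Parameters |
|---|---|
| 3.2 and 13.2.2, endpoint sentence | Ktrans and IAUGC primary |
| 13.2.2, model, SDs and power | Ktrans and v_e |
| 9.1, extracted parameters | Examples given: Ktrans, v_e and τi; IAUGC not mentioned |
| Appendix 14.1.2, primary endpoints | Ktrans and/or IAUGC |
| Appendix 14.1.2, secondary endpoints | v_e among others |

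The appendix also says that both Ktrans and IAUGC require tumour T1 measured immediately before contrast uptake. It only strongly recommends a pre-contrast T1 map, and section 9.1 does not mention one.

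**The case against.** The strongest reply is that nothing depends on this figure. The 25 patients come from the pathologic response endpoint in 13.1.2, DCE-MRI is a secondary objective, and the error runs in the safe direction because the stated power is too low for the stated effect. All of that stands and limits the weight of the point. That a null result would be wrongly excused is a risk, not something the protocol says.

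A reader might infer that 71% belongs to a 0.5 SD change and that the protocol is out by a factor of two. The document does not support this. The match needs the normal approximation and an SD of differences (or a correlation of exactly 0.5), and two independent groups of about 12.5 give the same 70.5%. Nor is 71% against 92% to 99.8% a factor of two in power. For the same reason the sentence should not simply be changed to 67% power for 0.5 SD of the differences. The section derives only between-patient SDs, and with those a 0.5 SD change has 40%, 50%, 67% or 92% power (exact t) at correlations of 0, 0.25, 0.5 or 0.75.

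On endpoints, Ktrans is primary, modelled and powered throughout; the protocol never calls v_e primary; and the appendix's and/or wording would allow Ktrans alone. A fuller IAUGC analysis may sit in a statistical analysis plan not shown here. So a reader should not infer that v_e has been promoted, or that the imaging endpoint is open to choice after the data are seen. What remains is a contradiction between the endpoints named and the parameters modelled within one section.

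**Conclusion.** The power statement is wrong as written. For a paired comparison in 25 patients at two-sided 5%, power for a 1.0 SD change is at least 92% with the derived between-patient SD and a non-negative correlation, and 99.8% with the SD of change, against the stated 71%. This rests on an assumed alpha, sidedness and correlation range, because the section gives none; none of the variations tried, short of a strongly negative correlation, brings the figure down to 71%. The source of the 71% cannot be identified.

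The mismatch between the named endpoints (Ktrans, IAUGC) and the modelled ones (Ktrans, v_e) is also real. Both defects are minor: they affect a secondary objective, the power error is conservative, and the sample size and primary analysis are unaffected. They are worth correcting because the correction is cheap.

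**What to change.** Replace the power sentence in 13.2.2 with, for example: *Assuming a two-sided 5% test and a non-negative pre/post correlation, 25 patients give at least 92% power to detect a change of 1.0 between-patient SD (0.24 for Ktrans, 12.38 for v_e).* If a different effect size was intended, recompute for it and state alpha, sidedness, which SD is meant and the assumed correlation.

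Reconcile the endpoints across 3.2, 9.1, 13.2.2 and the appendix: apply the mixed model to Ktrans and IAUGC, label v_e secondary, and list IAUGC among the outputs in 9.1. First confirm that the acquisition in 9.1 includes the pre-contrast T1 measurement that the appendix requires. If IAUGC becomes a powered endpoint, it needs its own SD, which the protocol does not give.

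The cost is a few sentences. No extra patients are needed. Whether IAUGC can be computed from the planned scans without changing the acquisition depends on the T1 check.
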